### **8.3 Adverse Event Reporting Requirements**

#### **8.3.1 Assessment of AEs**

Subjects will be evaluated for AEs at each visit with the NCI CTCAE v4.0.

Adverse events, SAEs, and other reportable safety events will be reported by the participant (or, when appropriate, by a caregiver, surrogate, or the participant's legally authorized representative).

The investigator and any designees are responsible for detecting, documenting, and reporting events that meet the definition of an AE or SAE as well as other reportable safety events. Investigators remain responsible for following up AEs, SAEs, and other reportable safety events for outcome.

The investigator, who is a qualified physician, will assess events that meet the definition of an AE or SAE as well as other reportable safety events with respect to seriousness, intensity/toxicity and causality.

#### **8.3.1 Recording of AEs**

All adverse events will be recorded on a patient specific adverse event log.

#### **AE Reporting**

Toxicity will be scored using CTCAE Version 4.0 for toxicity and adverse event reporting. A copy of the CTCAE Version 4.0 can be downloaded from the CTEP homepage (<http://ctep.info.nih.gov>). All adverse clinical experiences, whether observed by the investigator or reported by the patient, must be recorded, with details about the duration and intensity of each episode, the action taken with respect to the test drug, and the patient's outcome. The investigator must evaluate each adverse experience for its relationship to the test drug and for its seriousness. The investigator must appraise all abnormal laboratory results for their clinical significance. If any abnormal laboratory result is considered clinically significant, the investigator must provide details about the action taken with respect to the test drug and about the patient's outcome.

#### **Serious Adverse Event (SAE) Reporting**

Definition of SAE

A serious adverse event is one that at any dose (including overdose):

1. Results in death
2. Is life-threatening\*
3. Requires inpatient hospitalization or prolongation of existing hospitalization
4. Results in persistent or significant disability or incapacity§

5. Is a congenital anomaly or birth defect

6. Is an important medical event¶

\* “Life-threatening” means that the subject was at immediate risk of death at the time of the serious adverse event; it does not refer to a serious adverse event that hypothetically might have caused death if it were more severe.

§ “Persistent or significant disability or incapacity” means that there is a substantial disruption of a person’s ability to carry out normal life functions.

¶ Medical and scientific judgment should be exercised in deciding whether expedited reporting is appropriate in situations where none of the outcomes listed above occurred. Important medical events that may not be immediately life-threatening or result in death or hospitalization but may jeopardize the patient or may require intervention to prevent one of the other outcomes listed in the definition above should also usually be considered serious. Examples of such events include allergic bronchospasm requiring intensive treatment in an emergency room or at home, blood dyscrasias or convulsions that do not result in inpatient hospitalization, or the development of drug dependency or drug abuse. A new diagnosis of cancer during the course of a treatment should be considered as medically important.

#### **Reporting of SAE to Institutional Review Board (IRB)**

All SAEs occurring on this study will be reported to the IRB according to the IRB policy.

## **9. STATISTICAL CONSIDERATIONS**

### **9.1 Sample Size Estimation**

Sample size is defined considering CRR as primary study endpoint. Based on the publication by Yamaguchi et al. CRR for newly diagnosed NKTCL with stage III-IV was 40% for regimen of SMILE. Thus, 40% CRR from published study defines null hypothesis (H0) for our trial. The sample size of 20 pts will allow to demonstrate a 30% improvement of CRR from 40% (null hypothesis, H0) with a type 1 error rate=0.05 (two-sided) and power=0.80. Sample size will be 22 under consideration of drop off rate for 2 subjects.

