|---------------------------------------|---------------------------------------------------------------------------------------------------------------------------------------------------------------------------------------------------------------------------------------------------------------------------------------------------------------------------------------------------------------------------------------------------------------------------------------------------------------------------------------------------------------------------------------------------|
|                                       | 
Sintilimab 200mg administered intravenously on Day 2 of each 21-day cycle for 6 cycles in induction treatment.
 
Sintilimab maintenance
 
Sintilimab 200mg administered intravenously on Day 1 of each 21-day cycle for up to 28 cycles in maintenance treatment.
 
Response assessment
 
Response will be evaluated according to 2014 Lugano criteria and 2016 Refinement of the Lugano Classification lymphoma response criteria in the era of immunomodulatory therapy using CT scan and PET-CT scan.
 |
| NUMBER OF PARTICIPANTS WITH RATIONALE | 22 patients                                                                                                                                                                                                                                                                                                                                                                                                                                                                                                                                       |
| STATISTICAL CONSIDERATIONS            | 
Sample size is defined considering CRR as primary study endpoint. Based on the publication by Yamaguchi et al. CRR for newly diagnosed NKTCL with stage III-IV was 40% for regimen of SMILE. Thus, 40% CRR from published study defines null hypothesis (H0) for our trial. The sample size of 20 pts will allow to demonstrate a 30% improvement of CRR from 40% (null hypothesis, H0) with a type 1 error rate=0.05 (two-sided) and power=0.80. Sample size will be 22 under consideration of drop off rate for 2 subjects.
              |

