#### **9.2.1 Efficacy Analysis**

##### **Analysis Populations**

Main and secondary study objectives will be assessed with an intent to treat analysis. (i.e. all enrolled patients)

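### Two patients are added for drop-off although all enrolled patients are analysed, so the stated 80% power does not describe the prescribed analysis: about 81% with no loss, 61% in the worst planned case

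*Protocol*

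**What the plan says.** Section 9.1 takes the null rate from the published SMILE study: "Thus, 40% CRR from published study defines null hypothesis (H0) for our trial". The effect that the trial is meant to detect is then given in these terms: "The sample size of 20 pts will allow to demonstrate a 30% improvement of CRR from 40% (null hypothesis, H0"). The error rates and the allowance for losses come next: "with a type 1 error rate=0.05 (two-sided) and power=0.80. Sample size will be 22 under consideration of drop off rate for 2 subjects". The synopsis carries the same text.

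Section 9.2.1, under Analysis Populations, fixes who is analysed: "Main and secondary study objectives will be assessed with an intent to treat analysis. (i.e. all enrolled patients"). The primary outcome in section 5.1 is CRR at the end of cycle 6. The design in section 6.1 is single arm, so the comparison is a one-sample test of a proportion against 40%. The protocol does not name that test, give a critical number of CRs, or say how a patient without a cycle 6 assessment is counted.

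**The concern.** Enlarging a sample for drop-off works when those who drop off are removed and the analysis is run on the rest. Here 22 would be enrolled so that 20 remain. Section 9.2.1 does not remove them. A patient who is lost before the end of cycle 6 without a CR adds one to the denominator and nothing to the numerator. The two extra patients then do not protect the power; each loss lowers the observed rate.

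The power statement and the analysis set therefore describe two different analyses. This bears on how the trial is read. With 13 CRs, 13 of 20 evaluable patients is significant (upper tail 0.021), while the same 13 of 22 enrolled is not (0.055). A text that sizes the trial on one denominator and analyses the other leaves room for dispute once the results are known. The trial is also described as preparation for a larger randomised study, so its planned chance of success should be stated for the analysis that will be run.

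**Working it through.** **Inputs.** p0 = 0.40, two-sided alpha 0.05 (0.025 in the upper tail), power 0.80, n = 20, two drop-offs and 22 enrolled, all from section 9.1. The analysis set is all enrolled, from section 9.2.1. p1 = 0.70 is the absolute reading of the 30% improvement.

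**Step 1: reproduce the plan's figure.** The one-sample normal approximation is

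n = [z(0.975)·√(p0·q0) + z(0.80)·√(p1·q1)]² / (p1 − p0)²

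= [1.960 × 0.4899 + 0.8416 × 0.4583]² / 0.30² = 1.3459² / 0.09 = 20.13.

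Power at n = 20 is Φ[(0.30·√20 − 1.960 × 0.4899) / 0.4583] = Φ(0.832) = 79.7%. The stated 20 patients and 0.80 are recovered to rounding.

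**Step 2: actual rejection probability at n = 20.** The smallest count with upper tail at most 0.025 under 40% is 13: P(X ≥ 13 | 20, 0.40) = 0.0210. Power is P(X ≥ 13 | 20, 0.70) = 0.772. This does not depend on choosing an exact test. For the z-test the standard error under the null is √(0.24/20) = 0.1095; 12 CRs give z = 0.20/0.1095 = 1.83 and 13 give z = 0.25/0.1095 = 2.28. The cut-off is again 13, so the power is again 77.2%.

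**Step 3: the prescribed analysis, n = 22.** The cut-off is 14: P(X ≥ 14 | 22, 0.40) = 0.0215, while 13 gives 0.055. The z-test agrees, since 13 of 22 gives z = 1.83. If k enrolled patients are certain non-CRs and the others each have a 70% chance of CR, power is P(X ≥ 14 | 22 − k, 0.70).

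| Additional losses counted as non-CR | Formula | Power | Chance of missing |
|---|---|---|---|
| 0 | P(X ≥ 14 given 22, 0.70) | 81.4% | 18.6% |
| 1 | P(X ≥ 14 given 21, 0.70) | 72.3% | 27.7% |
| 2 (as allowed for in 9.1) | P(X ≥ 14 given 20, 0.70) | 60.8% | 39.2% |

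The last row is easy to see directly: 20 × 0.70 = 14 expected CRs, exactly the number needed. The rate over all enrolled has fallen to 14/22 = 63.6%. For it to stay at 70% with two certain failures, the other 20 would need a CRR of 0.70 × 22/20 = 77%.

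**The case against.** The strongest reply is that nothing has been miscalculated. A reader might infer from the 77% that the 80% is an arithmetic slip. Step 1 shows otherwise: the figure comes from a standard approximation, and the gap of 2.8 points to 77.2% is the discreteness of the binomial. Nor is 77% the power of this trial, because it belongs to a 20-patient analysis that section 9.2.1 does not prescribe. This stands.

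A reader might also infer that the trial simply has 61% power. The protocol does not support that either. The figure needs both allowed-for drop-offs to occur, both to count as non-CR (usual under intent to treat, but not stated), and the 70% to apply only to the other 20. Section 9.1 names no denominator for its rate. If 70% is the rate among all enrolled, losses are already inside it and 81% holds. Section 6.1 also asks for a full assessment when a patient stops for progression or an adverse event. A patient who stops for progression is already among the expected 30% without CR, and adding that patient again would count one failure twice. The low figure fits only losses beyond that 30%.

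A third inference is that the 30% improvement is relative, giving 52% and power of only 17% at n = 20 or 19% at n = 22. The plan's own 20 patients rule this out, so only the wording needs tidying.

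Finally, the name of the test, the critical value and the handling of missing assessments are commonly left to a statistical analysis plan, so their absence is not itself a fault. The mismatch remains, because the protocol itself fixes both the allowance for drop-off and the analysis of all enrolled patients.

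**Conclusion.** The point holds as an inconsistency within section 9. The power of 0.80 is stated for 20 evaluable patients, where it is right by normal approximation (79.7%) and 77.2% in fact. The prescribed analysis covers all 22 enrolled, with at least 14 CRs needed, and there the power lies between about 61% and 81%. The upper end assumes a 70% CRR among all enrolled. The lower end assumes two additional losses counted as non-CR and 70% in the other 20. A regimen at 70% would thus miss significance about 2 times in 10 at best and about 4 in 10 in the worst planned case. The type 1 error is not affected: the upper tail at the cut-off is 0.0215, below 0.025.

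**What to change.** Keep 22 patients and revise section 9.1 and the synopsis together:

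- State the hypotheses as CRR 40% against 70%, an absolute difference of 30 percentage points.
- State an exact binomial test on all enrolled patients, with success at 14 or more CRs of 22 (upper tail 0.0215).
- State that a patient without an end-of-cycle-6 assessment counts as non-CR.
- Replace the sentence on 20 patients, power 0.80 and two drop-offs with power of 81% with no loss, 72% with one and 61% with two.

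This takes a few lines of text and no extra patients. The cost is a less favourable stated power. The rewrite makes the statement match the analysis; it does not raise the power. If the sponsor wants at least 80% even with two certain non-CRs, the smallest number that reaches it exactly is 30 (18 or more CRs, power 80.9%), which is 8 more patients. Exact power does not rise smoothly: at 31 it falls back to 77.1%.

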### **9.2 Analysis Plan**

The data will be analysed at the end of the study. No formal interim analyses are planned as the treatment is considered to be relatively safer than the standard therapy. However, analysis may be performed for conference presentations after all patients have been recruited and treated, but have not completed the follow-up time. This may only be done after recruitment of all patients and completion of treatment and hence unlikely to affect the study.

#### **9.2.1 Efficacy Analysis**

##### **Analysis Populations**

Main and secondary study objectives will be assessed with an intent to treat analysis. (i.e. all enrolled patients)

##### **Overall Response Rate**

Overall response rate is calculated as the sum of the complete and partial remission rates.

##### **Progression-Free Survival**

Progression-free survival (PFS) will be computed from the date of enrollment to the date of disease progression or relapse or date of death for any reason or censored at the date of the last follow-up visit up, whichever occurs earlier.

PFS curves will be generated by applying the Kaplan-Meier method.

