## 6. STUDY DESIGN AND STUDY POPULATION

### 6.1 General Study Design

This phase II, open-label, single arm trial will evaluate the efficacy and safety of anti-PD-1 antibody in combination with pegaspargase in treatment of newly diagnosed advanced stage NK/T-cell lymphoma.

All eligible patients will receive induction treatment for six cycles of Anti-PD-1 antibody sintilimab plus pegaspargase (21-day cycle) and sintilimab monotherapy maintenance treatment for about 2 years (21-day cycle).

The follow-up period will last up to 2 years from the date of last subject enrollment.

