#### Response assessment

Response will be evaluated according to 2014 Lugano criteria and 2016 Refinement of the Lugano Classification lymphoma response criteria in the era of immunomodulatory therapy using CT scan and PET-CT scan.

Patients will be evaluated for safety and tolerability of study treatment.

Anti-tumor activity assessment will be performed at cycle 3 and 6, every 4 months in the first year of follow-up, followed by every 6 months in the second year of follow-up (end of study).

For patients who experience PD or who discontinue the study due to an adverse event (AE) or a serious adverse event (SAE), the full assessment (EOT) should be obtained 30 days of the last dose of study treatment or before another anticancer therapy is initiated, whichever is shorter.

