## 8 STUDY ASSESSMENTS

### 8.1 Schedule of Events

**Table 3 Schedule of Events and related footnotes summarize information on the timing of study assessments.**

| Protocol Activities                                            | Pre-Treatment Assessment | Induction Phase              |                           | Maintenance Phase              |                                               | Follow-up Phase                |                     |
|----------------------------------------------------------------|--------------------------|------------------------------|---------------------------|--------------------------------|-----------------------------------------------|--------------------------------|---------------------|
|                                                                |                          | D1 (from Cycle 1 to Cycle 6) | EOI (14-21d from cycle 6) | D1 (from Cycle 7 to 34 cycles) | Evaluation (14-21d from cycle 12, 18, 24, 30) | EOT (within 30d from cycle 34) | FUP (every 4 month) |
| Informed Consent                                               | X                        |                              |                           |                                |                                               |                                |                     |
| Medical history                                                | X                        |                              |                           |                                |                                               |                                |                     |
| Bone marrow aspiration biopsies                                | X                        |                              |                           |                                |                                               |                                |                     |
| Tumor biopsies                                                 | X                        |                              |                           |                                |                                               |                                |                     |
| Pregnancy test (women of childbearing age)                     | X                        |                              |                           |                                |                                               |                                |                     |

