| HBV, HCV and HIV serology                                      | X                        |                              |                           |                                |                                               |                                |                     |
| Tumor Imaging (evaluation)                                     | X                        |                              | X                         | X                              | X                                             | X                              |                     |
| EORTC QLQ-C30                                                  | X                        |                              | X                         | X                              | X                                             | X                              |                     |
| Concomitant Medications                                        | X                        | X                            | X                         | X                              |                                               | X                              |                     |
| AEs Assessment                                                 |                          | X                            | X                         | X                              |                                               | X                              |                     |
| Survival                                                       |                          |                              |                           |                                |                                               | X                              | X                   |
| Pegaspargase                                                   |                          | X                            |                           |                                |                                               |                                |                     |
| Sintilimab                                                     |                          | X                            |                           | X                              |                                               |                                |                     |

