### 8.2 Assessment of Tumor response

Tumor response is classified according to 2014 Lugano criteria[21] and 2016 Refinement of the Lugano Classification lymphoma response criteria in the era of immunomodulatory therapy[22]. The objective efficacy is divided into complete

remission (CR), partial remission (PR), stable (SD), disease recurrence or disease progression.

Response will be assessed at the interim (C3) and the end (C6) of induction therapy and the every 6 cycles of sintilimab treatment until completion of maintenance phase (EOT visit).

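### PFS is censored at a visit rather than at a tumour assessment, and the protocol contradicts itself on whether follow-up visits include imaging; if they do not, 2-year PFS is somewhat overstated

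*Protocol*

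**What the plan says.** Section 9.2.1 measures PFS from enrolment to progression, relapse or "date of death for any reason or censored at the date of the last follow-up visit up, whichever occurs earlier". On estimation it adds "PFS curves will be generated by applying the Kaplan-Meier method". The same section censors overall survival at the last contact. Two-year PFS is a named secondary endpoint in the synopsis and in section 5.2.

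Three places describe tumour assessment:

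- **Section 6.1** has assessments at cycles 3 and 6, then "every 4 months in the first year of follow-up, followed by every 6 months in the second year of follow-up (end of study". It also requires a full end-of-treatment assessment after progression or a stop for an adverse event.
- **Section 8.2** has assessments at cycles 3 and 6 and then "the every 6 cycles of sintilimab treatment until completion of maintenance phase (EOT visit". It mentions none after that visit.
- **Table 3** marks tumour imaging before treatment, at end of induction, on Day 1 of the maintenance cycles, at the evaluations after cycles 12, 18, 24 and 30, and at end of treatment. The 4-monthly follow-up column is blank for imaging and for physical examination. Survival is the only row marked there.

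On the length of observation, section 6.1 says: "The follow-up period will last up to 2 years from the date of last subject enrollment".

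**The concern.** Death comes to light at any contact, but progression is usually found only when someone looks for it. Censoring PFS at a visit is harmless if each visit includes a tumour assessment. If it does not, the patient is carried in the risk set as progression-free through time in which progression could not have been seen.

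The patients exposed are those who leave treatment without progression and stay in follow-up. The protocol foresees them: it has permanent-discontinuation rules for toxicity (section 7.5), and it allows for patients who refuse further treatment but agree to be followed for disease status (section 6.2.3). A site working from Table 3 or 8.2 would stop scanning them at the end-of-treatment visit; a site working from 6.1 would not.

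At stake is the 2-year PFS from a single-arm study that the protocol calls preparatory for a larger randomised trial. Duration of response depends on the same scans.

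**Working it through.** The protocol gives no assumed PFS rate, event count or drop-out rate for PFS, so there is no figure of its own to reproduce.

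**1. Who is unscanned under Table 3, and for how long.** Inputs: 21-day cycles, 6 induction plus up to 28 maintenance cycles (sections 7.1 and 7.2), and end of treatment within 30 days of cycle 34 (Table 3). Two years is 730.5 days, and day 1 is cycle 1 Day 1.

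- Cycle 34 Day 1: 33 × 21 + 1 = day 694. End of cycle 34: 34 × 21 = day 714.
- The end-of-treatment visit falls between day 694 and day 724 if the 30 days run from Day 1 of cycle 34. It can be as late as day 714 + 30 = 744 if they run from the end of the cycle.
- On-schedule completer: at most 730.5 − 694 = 36.5 unscanned days before the 2-year mark, possibly none.
- Stop after cycle 6 (day 126), end-of-treatment scan about 30 days later (day 156): 730.5 − 156 = 574.5 days, about 19 months, with no planned scan.

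**2. Size of the overstatement if Table 3 and 8.2 are followed.** Assumptions, none of them in the protocol: exponential PFS with true 2-year PFS of 40-60%; a fraction d of 10-30% stopping without progression at months 2-12 (midpoint s = 7); exponential survival after progression with mean m of 8-16 months; no further scans after stopping; no progression found clinically; deaths counted as events. The 2-year estimate is then too high by d times the probability of progressing between s and 24 months and still being alive at 24 months. With λ = −ln(2-year PFS)/24 and μ = 1/m:

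excess = d · λ · e^(−24μ) · [e^(24(μ−λ)) − e^(s(μ−λ))] / (μ−λ)

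- *Low end* (PFS 60%, d = 10%, m = 8): λ = 0.0213, μ = 0.125, so 0.0213 × 0.0498 × (12.05 − 2.07)/0.1037 = 0.102. Times 0.10 gives 0.010, or 1 point.
- *High end* (PFS 40%, d = 30%, m = 16): λ = 0.0382, μ = 0.0625, so 0.0382 × 0.2231 × (1.793 − 1.186)/0.0243 = 0.213. Times 0.30 gives 0.064, or about 6 points.

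Simulation of 400,000 patients per scenario agrees: 0.612 against a truth of 0.602, and 0.464 against 0.400. If half of the unscanned progressions are found clinically, the excess halves, to about 0.5-3 points.

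**3. Both readings of the protocol.** A second simulation (200,000 per scenario) used the cycle calendar with true 2-year PFS of 50-70%, median survival after progression of 3-12 months, and 0-50% of progressions found clinically.

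| Scans done | Stop early without progression | Overstatement, points |
|---|---|---|
| Table 3 only | 0% | 0.1-0.3 |
| Table 3 only | 10% | 0.4-1.5 |
| Table 3 only | 20% | 0.7-3.0 |
| Table 3 only | 40% | 1.4-5.8 |
| Section 6.1 follow-up scans | 0-40% | 0.1-1.5 |

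**4. Does changing the censoring date alone cure it?** No. If PFS is censored at the last scan, no further scans are done, and later deaths still count as events, the patients who die stay in the analysis and those who live are removed early. With an administrative cut-off at month 30 (assumed) the estimate is then too low:

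| True PFS | Stop early | Mean survival after progression | Estimate vs truth |
|---|---|---|---|
| 60% | 10% | 8 months | 0.590 vs 0.600 |
| 40% | 30% | 16 months | 0.383 vs 0.400 |
| 40% | 30% | 8 months | 0.373 vs 0.400 |
| 60% | 30% | 8 months | 0.565 vs 0.599 |

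In the same model, last-scan censoring is unbiased only if deaths after the last scan are censored too.

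**The case against.** The strongest objection is that section 6.1 does schedule tumour assessments in follow-up. Table 3's 4-monthly follow-up interval matches the 6.1 interval for the first year, so a mark omitted from the table is at least as plausible as a survival-only design. If 6.1 is followed, most follow-up visits are tumour assessments and the rule does little harm. This stands. What can be shown is a contradiction between sections, with a bias that depends on which one the sites obey.

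A reader might infer that scanning simply stops with the cycles, so that 2-year PFS is inflated throughout and no planned scan supports the 24-month value. The documents do not support that. Section 6.1 contradicts the premise. The end-of-treatment scan can fall as late as about day 744, beyond 730.5, and section 7.4 allows cycles to start late, which would move it later still. On-schedule completers are scanned to about 2 years in any case.

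It is also fair that deaths remain events, that clinically evident progression would be recorded without a scan, and that an error of a few points is small beside the imprecision of 22 patients: the standard error at 50% is √(0.5 × 0.5/22), about 10.7 points. But the error under Table 3 runs in one direction, and scans that were not taken cannot be recovered at analysis.

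**Conclusion.** The concern holds in a limited form. The PFS censoring rule in section 9.2.1 is tied to the wrong date, and 6.1 conflicts with 8.2 and Table 3 on whether patients are imaged in follow-up.

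Under Table 3 and 8.2, 2-year PFS is overstated by about 1-6 points with 10-30% stopping early without progression and none found clinically, or about half that if half are found. Under 6.1 the error is about 0.1-1.5 points. All of these figures rest on assumptions about PFS, early stopping and survival after progression that the protocol does not supply.

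The effect comes mainly from early stoppers. PFS beyond 2 years and duration of response are more exposed than the 2-year value. PFS is a secondary endpoint with no test or threshold attached, and the complete response rate at cycle 6 and the sample size are unaffected. It should be fixed, but it does not threaten the trial's main conclusion.

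**What to change.** 1. Reconcile sections 6.1, 8.2 and Table 3 into one imaging schedule. Mark the follow-up assessments that 6.1 already describes under Table 3's follow-up column, for every patient without progression, on or off treatment. State when the follow-up years in 6.1 begin.
2. In section 9.2.1, censor PFS at the date of the last adequate tumour assessment, or at enrolment if there is none.
3. State in the same place how a death after one or more missed assessments is handled. Without such a rule, last-scan censoring can push the estimate down by 1-3 points.

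The first step does most of the work: with follow-up imaging in place, the last visit and the last assessment largely coincide.

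The cost is a few sentences and a corrected table. The scans are ones the protocol already describes in 6.1, though sites that have worked from Table 3 would have to add them. The reported PFS may be slightly lower.
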